### Missing data

Missing data will be reported for each variable and addressed through multiple imputation using chained equations (MICE) [44]. Assuming that data is missing at random, multiple imputation allows analysis of variables with missing data and is preferable to restricting analysis to only include those with complete data [45, 46]. The number of imputations will be determined based on the fraction of missing information (FMI) such that the number of imputations undertaken equals the percentage value of the FMI for example using 20 imputations if the FMI is 0.2 [44]. When the FMI is greater than 0.5, this relationship does not hold and greater than 100 imputations may be needed [47]. Given the uncertainty with multiple imputation when the FMI is greater than 0.5, if greater than 50% of cases having missing data, a complete case analysis will be undertaken for sensitivity analysis.

### Statistical analysis

Multivariable logistic regression will be used for model development rather than time-to-event methods such as the cox proportional hazards model. We expect to have complete outcome data for all participants at 12 months and have chosen the end points of 6- and 12-months for model development as these have particular clinical relevance. Using logistic regression to model these outcomes does not require an assumption of proportional hazards that may not apply to the prognostic indicators included in the model. The model will be developed through backwards elimination with a nominal level of alpha for variable exclusion set at 0.1 (10%). Using overly stringent levels of alpha for backwards elimination such as 0.05 is more likely to create an overly simplified model that eliminates relevant prognostic variables [48]. Non-linearity of continuous variables will be addressed by using a multivariable fractional polynomial approach, an established technique for transforming non-linear continuous variables when developing a backwards elimination model [49, 50]. The effect of exposure to the IMPETUS-D palliative care education intervention will be analyzed as an additional variable in multivariable analysis to assess whether the intervention influenced mortality. This approach does not require exclusion of those who received the intervention from model development reducing the potential for over-fitting of the model which is more likely to occur if model development is limited to the control group only [51]. A sensitivity analysis of model performance in both the intervention and control groups will also be undertaken.

Performance of the model will be assessed through calculating c statistics and receiver operating curves describing model discrimination for 6 and 12 months mortality. Internal validation will be undertaken using bootstrapping resampling methods [52], which account for bias due to over-fitting more accurately than split sample cross-validation approaches [53]. The model development process will be repeated in 400 bootstrap samples to allow calculation of optimism adjusted calibration slopes and c statistics. Internal calibration will be assessed through comparing observed and predicted event rates for each decile of risk predicted by the model and plotting flexible calibration curves using loess-based smoothers [54]. This approach is considered more informative than the Hosmer-Lemeshow test regarding potential miscalibration [55, 56].

In addition to the model building process, a narrative analysis will also be presented describing the cohort at baseline with regard to age, gender, time since admission to residential care, level of functional impairment on MDS-ADL scale, and comorbidity burden. The spread of mortality rates across RACFs involved in the study will also be examined to explore heterogeneity between facilities. To examine heterogeneity between study sites further, a leave-center-out cross-validation approach will be applied using each RACF as an individual center (*n* = 24) to allow analysis of variability in the developed model in settings of differing baseline mortality risk.

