## Methods

### Study design

This is a secondary analysis of a cohort of people with dementia from RACFs participating in a cluster-randomized trial of a simulation-based palliative care education intervention (IMPETUS-D) [16]. The cohort includes people with dementia living in RACFs in three states in Australia (Victoria, South Australia, and New South Wales) administered by a single-aged care provider. Residents do not receive any additional treatment or intervention through the IMPETUS-D program and participation is voluntary for all staff. Ethics approval for the study was obtained from the Melbourne Health Human Research and Ethics Committee (HREC/17/MH/336) as a component of the IMPETUS-D project ethics application. The study protocol has been designed in accordance with the TRIPOD statement for transparent reporting of the development of multivariable predictive models [17]. Prognostic indicator variables are extracted from RACF records retrospectively from the time of IMPETUS-D randomization using the date of most recent weight measurement as *t*0. Mortality will then be assessed prospectively for each resident at 6 and 12 months after *t*0.

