### Participants

The cohort will comprise a minimum of 900 residents with dementia. Only residents who have been admitted to the RACF for a period of at least 90 days prior to enrolment will be eligible for inclusion if they have a documented diagnosis of dementia based on ICD-10 dementia definitions. Evidence of moderate to severe dementia will be required for study inclusion based on the cognitive skills assessment contained within the Aged Care Funding Instrument (ACFI) and dementia FAST staging.

The ACFI is a mandatory assessment instrument used to determine care needs and funding allocation for all residents of RACFs in Australia. Cognitive skills within the ACFI are divided into four groups (A, B, C, D) based on increasing degree of impairment such that group A has minimal impairment and group D has the most severe level of impairment. People with dementia with cognitive skills classified as group C or D (moderate to severe cognitive impairment) will be eligible for inclusion in the study. ACFI assessment of cognition uses the Psychogeriatric Assessment Scales—Cognitive Impairment Scale (PAS-CIS). This scale has been demonstrated to correlate well with the Mini-Mental State Examination (*r* = −0.77) [19] with higher scores indicating more severe impairment. Those with a PAS-CIS score of 10-15 are classified as cognitive skills C and those with a score of 16 or above as cognitive skills D. If the PAS-CIS score is not complete, the resident will be included if the ACFI appraisal determines that the resident meets the criteria to be classified as cognitive skills C or D based on evidence that they need assistance with the performance of activities of daily living due to cognitive impairment. In addition to ACFI criteria, study participants will need to meet the criteria for FAST stage 6e dementia at study entry. FAST staging correlates well with the trajectory of cognitive decline in moderate to advanced stages of dementia [20, 21] and stage 6e has been chosen as it represents the threshold for transition to the most advanced stage of dementia (FAST stage 7) for whom prognostic information may be particularly clinically relevant.

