### Sample size

The study cohort will be derived from 24 RACFs comprising a minimum of 2400 residents receiving long-term care. Assuming that 50% of residents will have a diagnosis of dementia based on previous published data from long-term care in Australia [37], there will be an estimated minimum of 1200 residents with dementia. Three quarters (77.3%) of people with dementia in RACFs in Australia have moderate to severe cognitive impairment [38] equating to a minimum of 900 people with dementia who would meet the criteria for inclusion in the cohort.

A minimum of 10 events per variable has been proposed as a reasonable sample size for the development of predictive models [39] and increasing the sample size to 20 events per variable appears to improve the reliability of results [40]. For the ten prognostic indicator variables, a minimum of 200 events (deaths) are therefore required to reach a minimum of 20 events per variable. In RACFs in Australia, the 12-month mortality rate for people with dementia is approximately 30% [37], which is similar to mortality rates found in cohort studies of people with dementia in long-term care in the USA [41, 42]. Assuming a mortality rate of 30%, the required minimum cohort size for the model development cohort is therefore 667 people with dementia to observe a minimum of 200 deaths.

An alternative method for estimating the minimum sample size required for model development has been recently proposed by Riley et al. [43]. Using the optimism corrected c statistic for 12-month mortality reported for the ADEPT model (*c* = 0.68) [42], a *R*^2^_D_ value of 0.208 can be derived. This value can then be used to estimate sample size when combined with a prespecified level of shrinkage for the final model along with the expected event rate and the number of candidate predictor variables. Using the pmsampsize package in R version 3.6.2 with an *R*^2^ of 0.208, shrinkage factor of 0.9, event rate of 0.3, and 10 predictor variables gives a minimum sample size of 381 with 11.43 events per variable. The estimated minimum study cohort of 900 people will therefore exceed this figure and also the more conservative 20 events per variable estimate.

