### Reporting of results

Results will be reported in accordance with the Tripod checklist for reporting studies developing multivariable predictive models [17]. The flow of participants through the study will be presented along with their baseline characteristics and the number of participants with missing data. The distribution of participants between intervention and control arms of the IMPETUS-D palliative care education trial will be reported and analysis of the effect of exposure to the intervention on mortality outcomes will be reported. The unadjusted association between each predictor variable and mortality outcomes will be presented in addition to the results of the multivariable analysis and details of how the final prediction model was developed.

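### The mortality effect of a facility-randomized intervention is to be estimated as a covariate in logistic regression with no stated allowance for the 24 facilities, so its standard error would be too small if facilities differ

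*Protocol article*

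**What the plan says.** The protocol article's Study design section draws the cohort "from RACFs participating in a cluster-randomized trial of a simulation-based palliative care education intervention". Under Sample size, "The study cohort will be derived from 24 RACFs comprising a minimum of 2400 residents receiving long-term care"; under Participants, "The cohort will comprise a minimum of 900 residents with dementia".

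The Statistical analysis section chooses multivariable logistic regression, with backward elimination at 0.1 and fractional polynomials for continuous predictors. Exposure to the intervention then "will be analyzed as an additional variable in multivariable analysis to assess whether the intervention influenced mortality". The same paragraph plans a sensitivity analysis of how the model performs in each arm. Reporting of results makes the exposure effect a promised result: "analysis of the effect of exposure to the intervention on mortality outcomes will be reported".

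Facilities enter the analysis in two places, both in the Statistical analysis section. First, "The spread of mortality rates across RACFs involved in the study will also be examined to explore heterogeneity between facilities". Second, a leave-center-out cross-validation over the 24 facilities is meant to show how the model varies where the underlying risk of death differs. The article states no random facility effect, GEE, cluster-robust variance or ICC.

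**The concern.** Because the intervention was randomized by facility, the information about its effect comes from 24 units, not from about 900 residents. A standard logistic regression treats residents as independent given the covariates. If residents of the same facility share some remaining risk of death, the model-based standard error of the exposure term is too small, its confidence interval too narrow and its p-value too low.

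The article itself expects facilities to differ in mortality, but the two steps it assigns to that variation are one descriptive and one predictive. Neither feeds back into the error of the exposure term.

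At stake is a published statement on whether a palliative care education programme changed mortality. Chance differences between facilities could be read as such an effect, in either direction.

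**Working it through.** **The plan's own figures.** The article gives no figure for the precision of the exposure effect. Its sample-size figures reproduce:
- 200 / 0.30 = 666.7, rounded up to 667.
- 10 / [(0.9 − 1) × ln(1 − 0.208/0.9)] = 380.5, rounded up to 381, and 381 × 0.3 / 10 = 11.43 events per variable.

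These concern the prediction model and do not bear on the point.

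**Inputs from the article.** 24 facilities (Sample size), at least 900 residents (Participants), and 12-month mortality of about 30% (Sample size).

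**Assumptions.** The article gives neither the ICC nor the allocation ratio. I take a residual ICC of 0.005 to 0.05, 12 facilities per arm, and equal facility sizes.

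**Formulas.**
- Mean facility size: m = 900 / 24 = 37.5.
- Design effect: DE = 1 + (m − 1) × ICC = 1 + 36.5 × ICC.
- Ratio of true to model-based standard error: √DE.
- Actual two-sided error of a nominal 5% test: 2 × [1 − Φ(1.96 / √DE)].
- Model-based standard error of the log odds ratio, unadjusted, with 450 residents per arm: √[2 / (450 × 0.3 × 0.7)] = √(2 / 94.5) = 0.145.

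| Assumed residual ICC | DE | √DE | SE of log OR | Actual error at nominal 5% |
|---|---|---|---|---|
| 0 | 1.00 | 1.00 | 0.145 | 5.0% |
| 0.005 | 1.18 | 1.09 | 0.158 | 7.2% |
| 0.01 | 1.37 | 1.17 | 0.170 | 9.3% |
| 0.02 | 1.73 | 1.32 | 0.191 | 13.6% |
| 0.05 | 2.83 | 1.68 | 0.245 | 24.4% |

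The 30% mortality figure enters only the column for the standard error of the log odds ratio. For a given ICC, the ratio and the error rate do not depend on it, so they apply equally to the 6-month outcome.

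**Smaller cohort.** With the minimum of 667 residents, m = 27.8. At ICC 0.01, 0.02 and 0.05 the ratio is 1.13, 1.24 and 1.53, and the actual error 8.2%, 11.4% and 20.0%.

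**Simulation check.** Beta-binomial deaths were generated in 24 facilities of 37 or 38 residents, 12 per arm, at 30% mortality with no intervention effect (3000 replicates per ICC). The resident-level test rejected in 5.0%, 9.2%, 14.0% and 22.4% of replicates at ICC 0, 0.01, 0.02 and 0.05. A t-test on facility proportions with 24 − 2 = 22 df rejected in 5.1%, 4.8%, 4.9% and 4.8%.

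**The case against.** The best defence is that the article is silent on the variance, not wrong. It does not say that residents are treated as independent, and a logistic model with a random intercept or a robust variance would fit its wording. It is also a condensed account, and a fuller plan may settle the matter. This stands in part: a reader might infer that the plan has decided to ignore clustering, and the text does not say so. But the article names the model, says how exposure enters it, gives the inferential purpose and promises the result. It is specific on lesser matters, such as the elimination level and the number of bootstrap samples. A reader who follows it as written would get the wrong standard error.

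A second defence is that the size is conditional. That is correct. No ICC is given, all facilities belong to one provider, and the resident-level covariates may lower the residual ICC. The table is an unadjusted two-arm comparison.

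Three stronger readings are tempting, and the article does not support them:
- **That the bootstrap resamples residents.** No resampling unit is stated.
- **That the arm term faces elimination at 0.1 and could stay in the risk equation by chance.** Exposure is not among the ten candidates in Table 1. It is introduced separately, which is compatible with a term that is forced in.
- **That pooling the arms rests on the result of this test.** The stated reasons are that exposure is included as a variable and that a control-only model would be more prone to over-fitting. A check of performance in each arm is also planned.

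Finally, the objective is a prediction model, which the Discussion calls preliminary. The exposure effect is secondary, and this limits how serious the point is.

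**Conclusion.** The point holds for one estimate: the effect of the facility-randomized intervention on 6- and 12-month mortality. No facility term or cluster-robust variance is stated for it, and the facility-level steps that are planned do not supply one. At an assumed residual ICC of 0.01 to 0.05, the standard error would be too small by a factor of 1.17 to 1.68, and a nominal 5% test would have about 9% to 24% type I error. At an ICC of 0 there is no inflation. The article expects differences between facilities but gives no size for them, so the range is illustrative.

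The c statistics and the sample-size figures are not affected. This is a correction to a secondary analysis, worth making before the effect is reported, and not a flaw in the main objective.

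**What to change.** State in the Statistical analysis section how the error of the intervention effect accounts for facility. Choose one of these in advance:
- logistic regression with a random intercept for facility;
- GEE with a robust variance corrected for the small number of clusters;
- a cluster-level analysis on about 22 df.

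Alternatively, report mortality by arm descriptively, without a p-value or any claim of effect. In either case, add a sentence saying that the arm term is kept outside the backward elimination.

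The cost is some analysis code and a short paragraph; no new data are needed. The downside is a wider confidence interval for the intervention effect. If a fuller analysis plan already contains such an adjustment, a sentence in the article that says so is enough.

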### Reporting of results

Results will be reported in accordance with the Tripod checklist for reporting studies developing multivariable predictive models [17]. The flow of participants through the study will be presented along with their baseline characteristics and the number of participants with missing data. The distribution of participants between intervention and control arms of the IMPETUS-D palliative care education trial will be reported and analysis of the effect of exposure to the intervention on mortality outcomes will be reported. The unadjusted association between each predictor variable and mortality outcomes will be presented in addition to the results of the multivariable analysis and details of how the final prediction model was developed.

## Discussion

This study aims to develop a mortality prediction model for people with dementia using prognostic indicators assessed during routine care provided in Australian RACFs. Rather than previous models that have been developed from minimum data set (MDS) variables in the USA, this model will be developed from predefined prognostic indicator variables that may better identify people with dementia at an increased risk of mortality. We believe the inclusion of variables that identify features of recent health instability such as infections, falls, and hospitalizations will identify people with dementia whose health is deteriorating better than a model that only includes factors describing health status at the time of assessment.

One of the limitations of this study is that prognostic indicator variables will be collected retrospectively from RACF files and there is a risk of under detection of variables if documentation is incomplete. While relying on routinely documented clinical information as the source of prognostic information has limitations, this approach reflects how the model would likely be used in clinical practice. A model that requires additional prospective assessment of residents outside of usual care is unlikely to be implemented in the RACF care environment in Australia given that uptake of prospective assessment tools for aspects of dementia care such as pain and behavioral assessment has been very limited unless mandated for use [57, 58].

The developed model should be considered preliminary and not be incorporated into clinical care without further study. In the current study design, heterogeneity in the duration of time the cohort has been living in long-term care at study entry (*t*0) may introduce survivorship bias. People with dementia newly admitted to long-term care have higher mortality rates within the first 3 months [42, 59] and excluding this group aims to develop a model that only applies to survivors of this high-risk period. To address the issue of survivorship bias, further study is needed involving a cohort followed prospectively from 3 months after RACF admission. Future research combining serial assessment of prognostic indicator variables with dynamic modeling techniques would also allow the model to be utilized across multiple time points. Comparing the performance of the developed model to the ADEPT model in an Australian RACF cohort will also be an important aspect of further validation of the model. The variables required for the ADEPT model are not routinely assessed during clinical care at RACFs in Australia and require additional assessment of residents that is beyond the scope of this model development study.

Even after further validation, there will always be uncertainty with predictive models and the aim is to provide guidance about potential illness trajectory to health care providers rather than replace clinical judgment. It is hoped that, once externally validated, a clinical tool could be developed to enable better identification of residents with dementia at greatest risk of mortality over the following 12 months for whom access to resources such as specialist geriatric medicine and palliative care support may be most critically needed to optimize care and facilitate anticipatory end of life care planning. Future development of a decision support tool would require the involvement of health professionals working in RACFs, people with dementia, and their caregiver’s in order to ensure that mortality risk information is utilized appropriately to meet the needs of the population that the tool intends to support.

## Data Availability

Not applicable.
